## Abstract

**Background:** Several studies have demonstrated that using a higher dose of statin can easily induce liver injury and myopathy. Low-density lipoprotein cholesterol (LDL-C) is a well-established modifiable risk factor for cardiovascular disease; however, the large majority of Chinese patients cannot meet the target level of LDL-C recommended by the Chinese expert consensus. Evolocumab has been demonstrated to reduce LDL-C by approximately 60% in many studies. Nevertheless, whether combined evolocumab and moderate-intensity statin is as effective in lowering LDL-C and decreasing incidence of MACE in Chinese patients presenting with the acute phase of acute coronary syndrome (ACS) remains unknown. Therefore, the “Evolocumab added to Moderate-Intensity Statin therapy on LDL-C lowering and cardiovascular adverse events in patients with Acute Coronary Syndrome” (EMSIACS) is conducted.

**Methods:** The EMSIACS is a prospective, randomized, open-label, parallel-group, multicenter study involving analyzing the feasibility and efficacy of evolocumab added to moderate-intensity statin therapy on lowering LDL-C levels in adult Chinese patients hospitalized for acute phase ACS. The sample size calculation is based on the primary outcome, and 500 patients will be planned to recruit. Patients are randomized in evolocumab arm (evolocumab 140mg every 2weeks plus rosuvastatin 10mg/day or atorvastatin 20mg/day) and statin-only arm (rosuvastatin 10mg/day or atorvastatin 20mg/day). The primary outcome is the percentage change in LDL-C in weeks 4 and week 12 after treatment. The secondary outcome is the occurrence of MACE after 12weeks and 1year of treatment.

**Discussion:** If the EMSIACS trial endpoints prove statistically significant, the evolocumab added to moderate-intensity statin therapy will have the potential to effectively lower subjects’ LDL-C levels, especially for the Chinese patients with acute phase ACS. However, if the risk of MACE is not significantly different between the two groups, we may extend follow-up time for secondary outcome when the clinical trial is over.

**Clinical trial registration**: The study is registered to ClinicalTrials.gov (NCT04100434), which retrospectively registered on November 24, 2020.

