## Materials and Methods

### Patient and Public Involvement

This is a prospective, open-label, randomized, parallel-group, and multicenter study. We are planning to include 500 patients with acute phase ACS (non-ST-segment elevation myocardial infarction (MI), acute ST-segment elevation MI within 24h of onset, and unstable angina within 72h of onset). Patients will be randomly assigned in a 1:1 ratio using a computer-generated random number system (block randomization with blocks of size 4 at random) and are divided into two treatment groups: statin-only therapy and evolocumab plus statin therapy. A 48-week follow-up study will be conducted.

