### Main Outcome Measures

Subjects of the present study will receive 24 treatments after being enrolled, and data of laboratory examinations will be evaluated at 72h and weeks 1, 4, 8, 12, 24, and 48 after intervention (Table 1; Figure 1).

The primary outcome of the present study will be the mean percentage change of the LDL-C level between baseline and weeks 4 and 12 post-treatment (Table 1; Figure 1). The secondary outcome will be MACE (defined as coronary heart disease death, nonfatal myocardial infarction, hospitalization for unstable angina, unplanned coronary revascularization, and stroke) assessed at week 12 and week 48 post-treatment (Table 1; Figure 1). The following issues will also be investigated: (1) the proportion of patients with LDL-C<70mg/dl, <55mg/dl and<40mg/dl during the study period; (2) patients’ quality of life as evaluated with the PROMIS 10 scale at week 12 and week 48 post-treatment; and (3) the percentage change in inflammatory biomarkers including but not limited to high-sensitivity C-reactive protein (hsCRP), interleukin (IL)-1β and IL-6, from baseline to weeks 48 (Table 1; Figure 1). Other biomarkers that exhibit significant difference between the two study arms will be investigated retrospectively after the trial.

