### Statistical Analysis

The primary efficacy analysis will be based on the time from randomization assignment to the first occurrence of any component of MACE. Data will be analyzed using intention-to-treat analysis (ITT) and per protocol (PP) to assess the efficacy and safety of evolocumab in combination with moderate-intensity statin therapy. The superiority of evolocumab will be assessed for all efficacy endpoint. Continuous variables with an approximately normal distribution will be reported with mean±standard deviation (mean±SD), and differences between the two treatment arms will be tested using independent sample t-test. For continuous variables that are not normally distributed, the median and interquartile range (IQR) will be given, and the nonparametric Mann–Whiney U test will be conducted to test for differences between treatment arms. Discrete variables will be reported with counts and percentage for each arm, and differences between arms will be examined using Fisher’s exact test. In order to compare MACE differences, Kaplan–Meier survival curve analysis will be performed, and hazard ratio (HR) and 95% CI will be calculated. Log-rank tests will also be performed to evaluate the differences in significance and verify treatment efficacy.

The ITT population will include all randomized patients and the PP population will include all randomized patients who complete the entire study. Subjects with missing data will be excluded from the corresponding analysis. Logistic regression will be used to analyze differences in the central effect sizes.

Results of the proposed study will be analyzed using SAS 9.2 or higher version (SAS Institute, North Carolina, United States) software. All statistical tests will be two-tailed unless otherwise indicated or presented with a 95% confidence interval (CI), and statistical significance will be established as *p*<0.05.

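### MACE follow-up may be extended because the MACE comparison is not significant; re-testing the longer data at 0.05 would give a false-positive rate of about 6.5% to 9%

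*Protocol article*

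**What the plan says.** All references are to the protocol article.

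- **Abstract, Discussion paragraph:** "if the risk of MACE is not significantly different between the two groups, we may extend follow-up time for secondary outcome" once the trial has finished. This is the only mention of an extension.
- **Patient and Public Involvement:** "A 48-week follow-up study will be conducted".
- **Main Outcome Measures:** MACE is the secondary outcome, "assessed at week 12 and week 48 post-treatment".
- **Statistical Analysis:** Kaplan–Meier curves and a hazard ratio with 95% CI are planned for MACE, and "Log-rank tests will also be performed to evaluate the differences in significance and verify treatment efficacy". On the level of the tests: "All statistical tests will be two-tailed unless otherwise indicated", and "statistical significance will be established as *p*<0.05".

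The standing of MACE varies within the article. The Abstract and Main Outcome Measures call it secondary. Aims of the Study makes the effect on MACE the first of two principal research questions. The opening sentence of Statistical Analysis bases the primary efficacy analysis on time to first MACE.

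**The concern.** A decision to lengthen follow-up can be harmless if it rests on a calendar date, a target number of events or a blinded event count. Here the stated trigger is the between-group MACE result itself. A significant result at the end of the trial would stand, while a non-significant one may lead to more follow-up. If the longer data are then tested at the same unadjusted level, the treatment has two chances to reach significance, and a later p-value below 0.05 no longer carries a 5% error rate.

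At stake is how far a MACE claim made after such an extension could be trusted, on an endpoint to which parts of the article give a leading role. The trigger is also likely to be met, because the Sample Size Calculation rests on LDL-C at week 4 and not on MACE.

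**Working it through.** **Inputs from the article.** Follow-up is 48 weeks. The MACE test is a two-sided log-rank test at 0.05, so the critical value is 1.96. Allocation is 1:1 with 250 patients planned per arm.

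**Inputs assumed.** The article gives neither an extension length nor a MACE rate. Let t be the number of events at week 48 divided by the number at the end of the extension; t is varied. Two further assumptions are that every non-significant 48-week result leads to an extension, and that the cumulative data are then tested once more at two-sided 0.05.

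**Step 1: the plan's own figures.** One two-sided test with |Z|>1.96 has a false-positive rate of 5%, the level stated. The enrolment figure also reproduces: 193/0.8 = 241.25, rounded up to 242 per arm and 484 in total. It concerns LDL-C and says nothing about MACE.

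**Step 2: two looks.** Under no treatment effect, the log-rank statistics Z1 (week 48) and Z2 (end of extension) are approximately bivariate normal with correlation √t. The overall rate is

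1 − P(|Z1| < 1.96 and |Z2| < 1.96).

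| Share of final events at week 48 (t) | Overall two-sided rate |
|---|---|
| 0.90 | 6.5% |
| 0.80 | 7.1% |
| 0.75 | 7.3% |
| 0.667 | 7.7% |
| 0.50 (events double) | 8.3% |
| 0.333 | 8.8% |
| 0.30 | 8.9% |

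A simulation with 4 million replicates gave 8.3% at t = 0.50 and 8.8% at t = 0.333. Two independent tests set the ceiling: 1 − 0.95² = 9.75%. As t approaches 1 the rate falls back towards 5%.

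These rates count false positives in either direction. Counting only false claims of benefit for evolocumab, the rate at t = 0.50 is 4.2%, against a nominal 2.5%.

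**Step 3: how likely the trigger is.** Assume a one-year control risk p of 10% to 20%, a hazard ratio of 0.8, and all 250 patients per arm followed.

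- Expected events: 250 × [p + 1 − (1 − p)^0.8]. At p = 0.10 this is 250 × (0.100 + 0.081) ≈ 45. At p = 0.20 it is 250 × (0.200 + 0.163) ≈ 91.
- Power by the Schoenfeld formula: Φ(√(d/4) × |ln 0.8| − 1.96), which is about 11% at 45 events and about 19% at 91.
- Events needed for 80% power: 4 × (1.96 + 0.842)² / (ln 0.8)² ≈ 631.

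Under these assumptions, a non-significant 48-week result is the expected outcome even if the treatment works.

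**Step 4: what restores 5%.** If both looks are to be confirmatory with the same nominal level, each must be tested at about 0.029 when t = 0.50, 0.032 when t = 0.667, or 0.028 when t = 0.333. A single test at a follow-up length fixed in advance keeps 0.05. So does a single confirmatory test at week 48 with the extension exploratory.

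**The case against.** The strongest defence is that the article never describes a second test. The sentence says only that follow-up may be extended. It stands in the Abstract alone, and the methods sections describe 48 weeks of follow-up and one time-to-first-event analysis. A descriptive post-trial follow-up is a fair reading. Alpha handling and the status of any extension may also be set out in the full protocol or SAP, which are not shown.

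Much of this stands. The second test is an inference. So is week 48 as the trigger point, which follows from the 48-week follow-up and from the extension being placed after the end of the trial. The word may makes the extension optional, so the calculated rates apply only if it is always carried out. Missing alpha spending is therefore not the point. The point is what the article does state: a rule that ties the extension to a non-significant comparison. An unseen document could limit the consequences, but it would not change that trigger.

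A reader might infer two stronger points, and the article supports neither.

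- **Week 12 as a further look.** MACE is to be assessed at week 12, but Statistical Analysis does not specify a separate significance test there. Any such multiplicity would also exist without the extension.
- **An extension that mixes time on and off study drug.** Drug Usage and Dosage describes treatment over the 1-year period, but nothing says what treatment patients would receive in an extension.

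**Conclusion.** The concern holds in a conditional form. The article states a result-dependent trigger for extending MACE follow-up, and that should be corrected. If the extension always followed a non-significant 48-week result and the cumulative data were re-tested at two-sided 0.05, the false-positive rate for MACE would be about 6.5% to 9%, and 8.3% if events double. The range rests on the assumption that week 48 holds 90% to 30% of final events; a shorter extension would inflate the rate less.

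It would go too far to say that the plan commits to a second test or has a fixed error rate above 5%. LDL-C, on which the trial is sized, is not affected. The point still merits action because the article elsewhere treats MACE as a principal question and as the primary efficacy analysis, and because the trigger is likely to be met.

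**What to change.** State in Statistical Analysis, and align the Abstract with it, that:

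- the 48-week log-rank and hazard ratio analysis is the only confirmatory MACE analysis;
- any extension prompted by its result is exploratory, covers all randomised patients, and is reported as a hazard ratio with confidence interval without a significance claim.

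If the sponsor wants a later confirmatory test, its timing and the alpha split should be fixed before the 48-week MACE data are seen. With two equally spaced looks and a common boundary, that means about 0.029 at each.

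The first option costs only wording and the loss of an unadjusted second chance at significance. The second costs some power at week 48, because the level there falls below 0.05, and it commits the sponsor to a follow-up time fixed in advance.

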## Introduction

In recent years, acute coronary syndrome (ACS) has been among the leading causes of cardiovascular death in China (Huo et al., 2017). It is characterized by fast onset, rapid development, poor prognosis, and high mortality (Gao et al., 2018). Abnormal lipid metabolism is one of the most significant risk factors of ACS. Elevated low-density lipoprotein cholesterol (LDL-C) is highly associated with adverse events such as cardiovascular disease, coronary artery disease, and major adverse cardiovascular events (MACE). Lowering LDL-C will reduce the risk of cardiovascular events (Sabatine et al., 2018). In recent years, LDL-C lipid-lowering therapy for the treatment of ACS and coronary heart disease (CHD) has been focused. Gao et al. (2014) systematically analyzed the effects of LDL-C lipid-lowering therapies on changes in the volume of coronary atherosclerotic plaque in patients with coronary heart disease and conducted evidence-based medical research supporting the application of LDL-C lowering therapies for clinical plaque treatment. Chinwong et al. (2015) suggested that achieving target LDL-C levels of <70mg/dl (<1.8mmol/L) in patients with ACS could significantly reduce the risk of cardiovascular events.

Expert consensus or guidelines have recommended treatment goals of LDL-C level. The 2019 ESC/EAS Guidelines for the management of dyslipidemias (Mach et al., 2019) stated that for patients at high risk, an LDL-C reduction of ≥50% from baseline and an LDL-C goal of <1.8mmol/L (<70mg/dl) are recommended; for patients at very-high risk, an LDL-C reduction of ≥50% from baseline and an LDL-C goal of <1.4mmol/L (<55mg/dl) are recommended. For the Chinese population, similar goal is proposed. According to the 2020 Chinese expert consensus on lipid management of very high-risk atherosclerotic cardiovascular disease patients (ASCVD patients; Atherosclerosis and Coronary Heart Disease Working Group of Chinese Society of Cardiology and Editorial Board of Chinese Journal of Cardiology, 2020), LDL-C level should be lowered to <55mg/dl (1.4mmol/L) AND reduction of LDL-C is ≥50% from baseline. For patients at very high-risk (defined as either having ≥2 serious ASCVD events or 1 serious ASCVD event combined with ≥2 high-risk factors), the double compliance of LDL-C lowering targets is required for achieving success in treatment for the Chinese population.

Statins have been widely used as an effective LDL-C lowering agent for ASCVD patients (Wang et al., 2017; Fox et al., 2018). However, many patients are unable to achieve the recommended LDL-C goal after high-intensity statin therapy (Wang and Fang, 2018). In addition, statins have the disadvantage of delayed onset of action (about 2weeks; Kakara et al., 2014; Koskinas et al., 2018). Genetic polymorphism associated with statin-induced myopathy in Chinese coronary artery disease patients (Liu et al., 2017). Several studies have demonstrated that using a higher dose of statin can easily induce liver injury (Alsheikh-Ali et al., 2007; Kasliwal et al., 2007; Chen et al., 2014; Naiqiong et al., 2017; Bandyopadhyay et al., 2018).

To achieve the target reduction in LDL-C, combinatory therapy using non-statin agents added to statin has been developed. Several recent trials have shown that the addition of either ezetimibe or anti-proprotein convertase subtilisin/kexin type 9 (PCSK9) monoclonal antibodies to statin therapy provides a further reduction in ASCVD risk, which is positively correlated with the incrementally achieved absolute LDL-C reduction (Giugliano et al., 2017, 2018; Schwartz et al., 2018; Koskinas et al., 2019). Current guidelines or expert advice have further recommended using PCSK9 inhibitors for high-risk or very high-risk patients given that the ezetimibe added to statin therapy failed to achieve the target LDL-C level. In the 2019 ESC/EAS Guidelines for the management of dyslipidemias (Mach et al., 2019), it is stated that for secondary prevention, patients at very high risk not achieving their goal on a maximum tolerated dose of statin and ezetimibe, a combination with a PCSK9 inhibitor is recommended. In the China cholesterol education program (CCEP) expert advice for the management of dyslipidemias to reduce cardiovascular risk (2019; China Cholesterol Education Program Working Committee et al., 2020), it is recommended to add PCSK9 inhibitors if the LDL-C goal of <55mg/dl (<1.4mmol/L) is not achieved after 4–6weeks of statin combined with ezetimibe therapy. In addition, for patients who may fail to achieve LDL-C<55mg/dl (<1.4mmol/L) with the ezetimibe added to statins therapy, PCSK9 inhibitors added to statins can be applied directly.

Evolocumab is a fully human monoclonal antibody against PCSK9. To date, several studies have been investigating the efficacy of evolocumab added to statin therapy in reducing the risk of cardiovascular events (Sabatine et al., 2017). It has been well demonstrated that evolocumab can effectively diminish dyslipidemia under various design settings (Raal et al., 2015; Koskinas et al., 2019). Nevertheless, whether the “evolocumab added to moderate-intensity statin” therapy is as effective in lowering LDL-C level in Chinese patients with acute phase ACS (i.e., the risk of recurrence of the event was extremely high within the first month of initial disease onset) remains to be elucidated. In addition, as statins may have side effects of liver damage, muscle pain, and increased risk of type 2 diabetes (Bandyopadhyay et al., 2018) and have favorable properties including anti-inflammation, platelet inhibition, and plaque stabilizing effects (Antonopoulos et al., 2012; Sikora et al., 2013; Camargo et al., 2014), comprehensive physical examination and laboratory blood tests including fasting glucose level, biomarkers of inflammation, liver and kidney functions panel, and platelet reactivity should be evaluated. Exploring these mechanistic effects can assist in advanced understanding of the clinical benefits of the present evolocumab on top of statin therapy.

### Aims of the Study

The overall purpose of EMSIACS study is to determine the feasibility, safety, and efficacy of the evolocumab added to moderate-intensity statin therapy, using the statin-only therapy as the control arm, on LDL-C level variability between baseline and 1-year follow-up in patients with acute phase ACS. This study was designed to address two principal research questions:

We determine the effects of the evolocumab added to moderate-intensity statin therapy on MACE.We plan to identify the appropriate ACS patient population for the administration of evolocumab in combination with standard statin therapy.

## Materials and Methods

### Patient and Public Involvement

This is a prospective, open-label, randomized, parallel-group, and multicenter study. We are planning to include 500 patients with acute phase ACS (non-ST-segment elevation myocardial infarction (MI), acute ST-segment elevation MI within 24h of onset, and unstable angina within 72h of onset). Patients will be randomly assigned in a 1:1 ratio using a computer-generated random number system (block randomization with blocks of size 4 at random) and are divided into two treatment groups: statin-only therapy and evolocumab plus statin therapy. A 48-week follow-up study will be conducted.

### Design and Setting

This trial has been registered in ClinicalTrials.gov (No. NCT04100434). The dates of the study estimated from January 1, 2021, to June 1, 2023.

This study will be conducted in the Tianjin Chest Hospital, China. Patients will be recruited from eight grade III Level A hospitals across the Tianjin area. The comprehensive analysis of baseline demographic characteristics, clinical examination, laboratory tests, and investigation of the forecast value will be conducted in the Tianjin Chest Hospital.

### Ethical Considerations

The study protocol has been reviewed and approved by the Ethics Committee (IEC) of the Tianjin Chest Hospital, China (No. 2019KY-019-01).

### Drug Usage and Dosage

The usage and dosage of evolocumab and statins used in the present study are as follows (Figure 1):

Statins: according to the recommendations of the 2020 edition of the Expert Consensus on Clinical Pathway of Blood Lipid Management in Patients with Acute Coronary Syndrome (Chinese Medical Doctor Association and Expert Group of Clinical Pathway of Lipid Management in Patients With Acute Coronary Syndrome, 2020), all patients with ACS are treated with moderate-intensity statins, rosuvastatin (10mg) or atorvastatin (20mg) daily throughout the study period.Evolocumab (trade name: Repatha®): patients will be given evolocumab within 72h immediately after diagnosis of ACS, with subcutaneous administration of 140mg evolocumab once every 2weeks (total 24 time points during the 1-year follow-up period). Use a single-use prefilled auto-injector to administer evolocumab subcutaneously in areas of the abdomen, thighs, or upper arms that are not tender, bruised, red or hardened. Within 30min, three injections will be given continuously with a single-use prefilled auto injector.

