### Data Collection and Management

Data will be recorded in Case Report Forms (CRFs) and entered into the clinical trial center by an electronic data capture system. Baseline data and data of different follow-up time points will be recorded. The schedule for the baseline assessment and subsequent assessments at different follow-up time points is shown in Table 1. Researchers on the trial management team will ensure the completeness and accuracy of the data. The trial manager, principal investigator, statisticians, and other members of the trial team will review the data cooperatively and complete the final definition and judgment of population analysis. The database will be secured.

**Table 1 tab1:** Schedule of treatments and assessments administered to patients.

Research stage	Screening stage	Follow-up treatment stage															
Visit (V)	V1	V2			V3	V4	V5	V6	V7	V8	V9	V10	V11	V12	V13	V14	V15
Date (D)	D-3 to D0	D1	D2	D3	D7	D14	W4 ± 3	W6 ± 3	W8 ± 3	W10 ± 3	W12 ± 3	W16 ± 3	W20 ± 3	W24 ± 3	W32 ± 3	W40 ± 3	W48 ± 3
Visit window																	
Inclusion/exclusion criteria	✓	✓															
Informed consent	✓																
Medial history	✓																
^*^Evolocumab treatment	✓																
Physical examination^(1)^	✓																
Vital signs^(2)^	✓	✓															
Blood routine^(3)^	✓				✓		✓				✓			✓			✓
Cardiac enzymes^(4)^	✓				✓		✓				✓			✓			✓
Blood lipids^(5)^	✓				✓		✓				✓			✓			✓
Blood sugar	✓				✓		✓				✓			✓			✓
hemoglobin A1c	✓						✓				✓			✓			✓
Liver function and renal function^(6)^	✓				✓		✓				✓			✓			✓
D-dimer	✓				✓		✓				✓			✓			✓
Uric acid	✓				✓		✓				✓			✓			✓
NT-proBNP	✓				✓		✓				✓			✓			✓
Thyroid function^(7)^	✓						✓				✓			✓			✓
High-sensitivity C-reactive protein	✓				✓		✓				✓			✓			✓
Ultrasound cardiogram	✓						✓				✓			✓			✓
PROMIS 10	✓										✓						✓

* Evolocumab is administered once every 2weeks.

(1) Physical examination: height and weight.

(2) Vital signs: body temperature, blood pressure and heart rate.

(3) Blood routine: RBC, WBC, platelet, and hemoglobin.

(4) Cardiac enzymes: creatine kinase (CK), CK-MB, troponin T (TnT), and Troponin (TnI)

(5) Blood lipids: low-density lipoprotein cholesterol (LDL-C), high-density lipoprotein cholesterol (HDL-C), very low-density lipoprotein cholesterol (VLDL-C), total cholesterol, triglycerides, apolipoprotein B, apolipoprotein A-1, lipoprotein (a), and free fatty acids.

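### The dosing section ends with three injections within 30 minutes, which does not fit the stated 140 mg evolocumab every two weeks

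*Protocol article*

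**What the plan says.** All statements are in the protocol article.

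- **Abstract:** the experimental arm receives "evolocumab 140mg every 2weeks plus rosuvastatin 10mg/day or atorvastatin 20mg/day".
- **Drug Usage and Dosage, dose sentence:** evolocumab starts within 72 hours of diagnosis, "with subcutaneous administration of 140mg evolocumab once every 2weeks (total 24 time points during the 1-year follow-up period").
- **Drug Usage and Dosage, next sentence:** the drug is given with a single-use prefilled auto-injector at one of three body sites.
- **Drug Usage and Dosage, last sentence:** "Within 30min, three injections will be given continuously with a single-use prefilled auto injector".
- **Data Collection and Management, Table 1 footnote:** "Evolocumab is administered once every 2weeks".
- **Main Outcome Measures:** "Subjects of the present study will receive 24 treatments after being enrolled". The primary outcome is the "mean percentage change of the LDL-C level between baseline and weeks 4 and 12 post-treatment".
- **Patient and Public Involvement:** "A 48-week follow-up study will be conducted".

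Injector strength is not stated. Figure 1, which the dosing section cites, is not available in the text reviewed.

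**The concern.** The last sentence is a positive instruction in the section that governs the investigational drug. It carries no condition, so a reader can take it in three ways: as applying to every administration, as a larger first dose, or as text left over from another schedule. The rest of the article does not settle which. Read literally, and with an injector that holds the full dose, it gives a patient three times the stated amount on one occasion.

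The timing matters. Week 4 is a primary time point and the one on which the sample size is based. Even a reading limited to the first dose changes the drug given before that measurement. Eight hospitals recruit, so different readings would make the dose vary by site within the experimental arm. The tested regimen could then not be described or reproduced with certainty.

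**Working it through.** **Inputs.** Dose 140 mg and interval 2 weeks (abstract; Drug Usage and Dosage). Number of administrations 24 (Drug Usage and Dosage; Main Outcome Measures). Follow-up 48 weeks (Patient and Public Involvement). Three injections (last sentence of Drug Usage and Dosage). Strength per injector: not stated.

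**1. The plan's own count.** Doses at weeks 0, 2, ..., 46 give 48 / 2 = 24 administrations, which matches the stated 24. The planned total is 24 × 140 = 3,360 mg.

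**2. Does another schedule explain the three injections?** Four-weekly dosing gives 48 / 4 = 12 administrations, not 24. A less frequent, larger dose therefore does not fit the rest of the text.

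**3. Amount per occasion.** Amount = injections × strength per injector.

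- To equal 140 mg, each injector would hold 140 / 3 = 46.7 mg. No such strength is stated.
- If each injector holds 140 mg (assumption), the amount is 3 × 140 = 420 mg.

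The range is 1 to 3 times the stated dose.

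**4. Cumulative amounts at an assumed 140 mg per injector.** The dose due on a sampling day is taken as given after the blood sample. Two doses then precede week 4 (weeks 0 and 2), and six precede week 12 (weeks 0 to 10).

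| Period | Planned | Three injections at first dose only | Three injections every time |
|---|---|---|---|
| Before week 4 | 2 × 140 = 280 mg | 420 + 140 = 560 mg (2.0 times) | 2 × 420 = 840 mg (3.0 times) |
| Before week 12 | 6 × 140 = 840 mg | 420 + 5 × 140 = 1,120 mg (1.33 times) | 6 × 420 = 2,520 mg (3.0 times) |
| All 24 doses | 3,360 mg | 420 + 23 × 140 = 3,640 mg (1.08 times) | 24 × 420 = 10,080 mg (3.0 times) |

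If the three injections together make up 140 mg, every cell equals the planned amount. These are milligrams administered; no effect on LDL-C is derived from them.

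**The case against.** The strongest reply is that the documents establish an unexplained sentence, not an overdose. The 140 mg figure appears only in the abstract and the dose sentence. The Table 1 footnote and Main Outcome Measures give an interval and a count, both compatible with three injections per occasion. Referring to a single-use auto-injector may name a type of device rather than a number of devices. Every amount above plan rests on an assumed strength. The section also fixes the dose at 140 mg, so read as a whole it need not authorise more. Finally, Figure 1 is not visible, the article condenses a fuller protocol, and sites may not dose from the article.

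Much of this limits the size of the point. The milligram projections are conditional, the footnote and the treatment count support only the interval and the number of occasions, and the device wording alone proves little. An explanation in Figure 1 or the full protocol cannot be excluded.

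The core remains. Condensing a protocol excuses omission, but this is an instruction that was included and does not fit the dose beside it unless the reader supplies a strength found nowhere in the text. Figure 1 is captioned as a study flowchart, and the sentence does not refer to it. If the sentence is a leftover, that is a reason to remove it.

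**Conclusion.** The concern holds: the last sentence of the dosing section is wrong as written. The probable intent is 140 mg every two weeks, which agrees with the abstract, the two-week interval in Table 1 and the count of 24. The three-injection sentence has no dose, visit or schedule to which it can belong.

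The consequence ranges from none to three times the stated dose per occasion, depending on injector strength and on how often the sentence applies. If an injector holds 140 mg, even the mildest reading doubles the amount given before the week 4 measurement. There is no evidence that three injections were given to anyone. Sample size, randomisation, endpoints and tests do not change. It should be corrected because it concerns the dose of the study drug and costs little to put right.

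**What to change.** Confirm the intent against the full protocol. If 140 mg every two weeks is the whole regimen, delete the last sentence of Drug Usage and Dosage; the abstract, the dose sentence, the Table 1 footnote and Main Outcome Measures need no change on this point. If a different first dose is intended, state its amount in milligrams, the number of injectors and the visit, and amend the regimen in the abstract and the dosing section to match.

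In either case, tell the eight hospitals which reading applies and check dispensing records for administrations of three injections. The cost is one sentence, one clarification letter and a records check.
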